**Methods:**

Protocol version 1.0, January 2026. This study is designed as a single-center, parallel-group randomized controlled trial. A total of 72 adolescents with depressive disorder who meet the eligibility criteria will be recruited and randomly assigned in a 1:1 ratio to either the intervention group or the control group. Participants in the control group will receive usual care, while those in the intervention group will receive additional VR-based intervention for 4 weeks (three sessions per week, approximately 25 min per session). Assessments will be conducted at baseline (T0), post-intervention (T1), and follow-up (T2). The primary outcome is the change in the 24-item Hamilton Depression Rating Scale (HAMD-24) score from T0 to T1. Secondary outcomes include the Hamilton Anxiety Rating Scale-14 (HAMA-14), Children’s Depression Inventory (CDI), Montreal Cognitive Assessment (MoCA), and heart rate variability (HRV) parameters (SDNN, RMSSD, LF, HF, and LF/HF). Data will be analyzed using linear mixed-effects models under the intention-to-treat principle.

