### Sample size

3.4

The sample size for this study was estimated based on data from Zeng et al. (2023). In that study, the post-intervention HAMD score was 21.30 ± 5.03 in the intervention group and 25.64 ± 5.39 in the control group, yielding an expected between-group difference (*δ*) of 4.34 points and an estimated pooled standard deviation (*σ*) of approximately 5.21. Using a two-sided significance level of *α* = 0.05 and a statistical power of 90% (*β* = 0.10), the required sample size was calculated using the formula for comparing the means of two independent groups. A minimum of 32 participants per group was estimated. Accounting for a potential dropout rate of 10%, the final sample size was increased to 36 participants per group, resulting in a total target sample size of 72 participants.

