### Outcomes

3.7

The primary outcome of this study is the change in the 24-item Hamilton Depression Rating Scale (HAMD-24) (Wiebe et al., 2022) score from baseline (T0) to post-intervention (T1). Assessments will be conducted by trained evaluators who are blinded to group allocation.

Secondary outcomes include: 1. Anxiety symptoms, assessed using the Hamilton Anxiety Rating Scale-14 (HAMA-14) (Li Y. et al., 2025); 2. Self-reported depressive symptoms (Li X. et al., 2025), assessed using the Children’s Depression Inventory (CDI); 3. Cognitive function (Jia et al., 2021), assessed using the Montreal Cognitive Assessment (MoCA). All psychological assessments will be conducted at baseline (T0), post-intervention (T1), and follow-up (T2). 4. Heart rate variability (HRV) parameters (Shapiro et al., 2007; Kircanski et al., 2019), including SDNN, RMSSD, low-frequency power (LF), high-frequency power (HF), and the LF/HF ratio, will be measured as objective physiological outcomes. Electrocardiogram signals will be recorded for at least 5 min under resting conditions in a quiet environment, and both time-domain and frequency-domain analyses will be performed.

Although the HAMD was originally developed for adults, it has been widely used in clinical studies involving adolescents with major depressive disorder and has demonstrated acceptable reliability and validity in adolescent populations (Zhao et al., 2023). Previous studies have shown that HAMD scores are significantly correlated with other well-established measures of depression severity in adolescents, supporting its clinical utility in assessing symptom severity and treatment response (Croarkin et al., 2021; Li et al., 2023). The HAMD is routinely used in psychiatric clinical practice, and our team has extensive experience in its administration. The scale has good sensitivity to symptom change and facilitates comparisons with previous depression trials. To enhance the assessment of depressive symptoms and address potential developmental limitations, the CDI—a developmentally appropriate self-report measure for children and adolescents—will also be administered at all assessment time points. The combined use of a clinician-rated scale and a self-report measure is expected to provide a more comprehensive assessment of the severity of depressive symptoms.

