### Statistical analysis

3.11

All statistical analyses will be performed using SPSS (version 26.0), with two-sided tests and a significance level set at *p* < 0.05. Baseline characteristics will be summarized using descriptive statistics. Continuous variables will be presented as mean ± standard deviation (SD) or median (interquartile range), depending on the data distribution, while categorical variables will be expressed as frequencies and percentages. Comparability of baseline characteristics between groups will be assessed using independent-samples *t*-tests, Mann–Whitney *U* tests, chi-square tests, or Fisher’s exact tests, as appropriate.

The primary outcome measure (HAMD-24 score) will be analyzed using linear mixed-effects models (LMM) to account for repeated measurements over time. Treatment group (intervention vs. control), time (T0, T1, and T2), and the group-by-time interaction will be specified as fixed effects. A subject-specific random intercept will be included as a random effect to account for within-subject correlations across repeated assessments. The group-by-time interaction will be considered the main parameter of interest for evaluating the intervention effect. Baseline values of the corresponding outcome measure will be included as covariates in the model to improve statistical precision and control for potential baseline differences. Estimated marginal means, mean differences, 95% confidence intervals, and associated *p*-values will be reported.

Secondary outcome measures, including the HAMA-14, CDI, MoCA, and HRV indices, will be analyzed using similar linear mixed-effects models. Given the exploratory nature of these secondary outcomes, the results will be interpreted with caution and considered hypothesis-generating.

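### The primary endpoint is the HAMD-24 change from T0 to T1, but the main parameter is a group-by-time interaction over T0, T1 and T2 that is not restricted to T1

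*Protocol article*

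**What the plan says.** The abstract states: "The primary outcome is the change in the 24-item Hamilton Depression Rating Scale (HAMD-24) score from T0 to T1". Section 3.7 (Outcomes) defines the primary outcome in the same way.

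Section 3.4 (Sample size) takes a post-intervention HAMD difference of 4.34 points and a pooled SD of about 5.21. It applies the two-independent-means formula at two-sided 0.05 and 90% power, giving 32 per group and 36 per group after 10% dropout.

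Section 3.11 (Statistical analysis) describes the primary model:
- Fixed effects: treatment group, "time (T0, T1, and T2), and the group-by-time interaction will be specified as fixed effects".
- Covariance: "A subject-specific random intercept will be included as a random effect".
- Baseline: "Baseline values of the corresponding outcome measure will be included as covariates in the model".
- Decision parameter: "The group-by-time interaction will be considered the main parameter of interest for evaluating the intervention effect".
- Reporting: "Estimated marginal means, mean differences, 95% confidence intervals, and associated" p-values, with no time point attached.

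No section makes the T1 contrast the deciding test or says that it is to be examined first.

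**The concern.** The endpoint and the sample size concern one time point. The parameter said to carry the intervention effect covers two post-baseline time points. With time as a three-level factor, the interaction consists of two contrasts, T1 minus T0 and T2 minus T0. A test of both together asks whether the group profiles differ at either visit.

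A difference that exists only at follow-up could therefore be reported as a positive result on the main parameter, although the declared primary endpoint shows nothing. Conversely, a T1 effect that partly fades could be missed by the interaction and found by the T1 contrast. Because the text leaves the contrast open, two defensible p-values would be available for the primary question once the data are seen.

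**Working it through.** **Inputs.** From section 3.4: difference 4.34, SD 5.21, two-sided alpha 0.05, power 90%, n = 32 per group before dropout. From section 3.11: three time points and a random intercept (compound symmetry). Assumed, because the article gives neither: within-subject correlation ρ of 0.3, 0.5 or 0.7, and the size of any T2 difference. SD 5.21 is taken at every visit, with complete data.

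**Step 1: reproduce the stated sample size.** Normal formula: n = 2(1.960 + 1.282)² × 5.21² / 4.34² = 30.28, so 31 per group. With the t distribution, power is 0.897 at 31 and 0.907 at 32, so 32 per group. Then 32 / 0.9 = 35.6, so 36 per group and 72 in total. The stated figures are reproduced by one two-group comparison at one time point.

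**Step 2: the 2-df interaction.** Let d1 and d2 be the true group differences in change from T0 at T1 and T2. The two contrast estimates have covariance (2/n) σ²(1−ρ) [[2, 1], [1, 2]], so the noncentrality is

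λ = n(d1² − d1·d2 + d2²) / [3σ²(1−ρ)],

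referred to F with 2 and 2(2n−2) = 124 df. Example with ρ = 0.5, d1 = 0, d2 = 4.34: λ = 32 × 18.84 / (3 × 27.14 × 0.5) = 14.8, power 0.936.

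**Step 3: the 1-df T1 change contrast.** Its standard error is √[4σ²(1−ρ)/n]. At ρ = 0.5 this is 1.302, and 4.34 / 1.302 = 3.33, giving power 0.911 by noncentral t on 124 df.

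**Results, 32 per group:**

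| True difference at T1 / T2 | Test | ρ = 0.3 | ρ = 0.5 | ρ = 0.7 |
|---|---|---|---|---|
| 0 / 4.34 | interaction, 2 df | 0.828 | 0.936 | 0.995 |
| 0 / 4.34 | T1 contrast | 0.05 | 0.05 | 0.05 |
| 0 / 2.17 | interaction, 2 df | 0.281 | 0.380 | 0.586 |
| 4.34 / 2.17 | interaction, 2 df | 0.702 | 0.847 | 0.975 |
| 4.34 / 4.34 | interaction, 2 df | 0.828 | 0.936 | 0.995 |
| 4.34 / any | T1 contrast | 0.798 | 0.911 | 0.990 |

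An effect fully lost by T2 (4.34 / 0) has the same λ, and so the same 2-df power, as a fully sustained one. At 36 per group the first row becomes 0.873, 0.960 and 0.998.

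**Step 4: simulation of the model as written** (random intercept, baseline covariate, 300 runs per scenario, T2-only difference of 4.34, 32 per group). The interaction was significant in 0.843, 0.967 and 0.993 of runs. It was significant with a non-significant T1 contrast in 0.790, 0.897 and 0.937. Some fits gave boundary or convergence warnings, so the closed-form figures are the main result. The two agree within about 3 points.

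**Step 5: time as a linear term instead.** With equal spacing, a T2-only difference of 4.34 would still give a significant slope interaction with probability 0.798, 0.911 and 0.990, so that coding does not remove the problem.

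**The case against.** The strongest reply is that section 3.11 never mentions a joint test, 2 df or a success rule. It speaks of a parameter in the singular. Read with the T0-to-T1 endpoint and the single-comparison sample size, the authors may well mean the group-by-T1 term, and a T1 comparison can be read from the promised marginal means. An analysis plan that is not shown could say so. What stands is that the joint 2-df test is the plain reading and not the article's wording. But this is more than a detail left for later: the article itself names a main parameter, and as printed that parameter is wider than its endpoint. If T1 is meant, the correction only records the intent.

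A T2-only effect of 4.34 points is also an extreme scenario that nothing in the article predicts. That is fair. It shows what the test responds to and is not a forecast, which is why the 2.17-point case is given beside it.

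A reader might infer more than the document supports:
- **Inflated type I error.** Under the global null, either test, fixed in advance, rejects 5% of the time.
- **A general loss of power.** The 2-df test loses when the effect halves by T2, but gains slightly when it is fully sustained or fully lost.
- **Rubin's rules cannot pool the interaction.** Section 3.11 only says that results will be combined by those rules. Nothing limits this to single parameters, and multi-parameter pooling exists.
- **A 4-df interaction, from the 1-, 2- and 3-month visits in the Discussion.** The stated model contains only T0, T1 and T2. How those visits relate to T2 is a separate question.

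**Conclusion.** The concern holds as a mismatch between stated items: endpoint and sample size at T1, main parameter over T0, T1 and T2. Followed as written, with time as a factor, the plan could declare an intervention effect with no T1 effect. The probability is 83% to 99.5% for a T2-only difference of 4.34 points and 28% to 59% for 2.17 points, against 5% for the T1 contrast. The power consequence runs both ways. If the effect halves by T2, the interaction has 70%, 85% and 97.5% against 80%, 91% and 99% for the T1 change contrast. If it is fully sustained, the interaction has 83%, 94% and 99.5%.

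These sizes rest on assumed correlations and T2 effects, equal SDs at each visit, compound symmetry and complete data. The T1 figures are for the unadjusted change contrast, not for a baseline-adjusted difference. The mismatch itself depends on none of these assumptions. It decides what counts as a positive trial, so it should be settled before unblinding.

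**What to change.** Add to section 3.11: the primary hypothesis is tested by the single 1-df between-group contrast for HAMD-24 change from T0 to T1 (the group-by-T1 term), two-sided at 0.05; the T2 contrast and the overall group-by-time test are secondary.

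The model must match that sentence. At present baseline HAMD-24 is both an outcome row (T0) and a covariate. If the change contrast is kept, T0 stays as an outcome row. If a baseline-adjusted T1 difference is preferred, keep baseline as a covariate, remove T0 from the outcome rows, and word the primary contrast as the adjusted group difference at T1.

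Cost: one sentence, plus the choice between these two model forms. No additional data are needed. The 72 participants stand, because the sizing already assumes a single post-intervention comparison.

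### The T0 HAMD-24 score is both a response and a covariate in the primary mixed model, so the interaction gains no baseline adjustment and the adjusted T1 difference gets intervals that are too narrow

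*Protocol article*

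**What the plan says.** Section 3.11 of the protocol article specifies the primary model term by term:

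- Fixed effects: "Treatment group (intervention vs. control), time (T0, T1, and T2), and the group-by-time interaction will be specified as fixed effects". T0 is a level of time, so the T0 score is one of the responses.
- Covariance: "A subject-specific random intercept will be included as a random effect to account for within-subject correlations across repeated assessments". No other structure is given.
- Target: "The group-by-time interaction will be considered the main parameter of interest for evaluating the intervention effect".
- Baseline: "Baseline values of the corresponding outcome measure will be included as covariates in the model to improve statistical precision", and also to control for baseline differences.
- Output: "Estimated marginal means, mean differences, 95% confidence intervals, and associated" p-values.

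The text does not restrict the response to T1 and T2, does not constrain the arms to a common mean at T0, and has no baseline-by-time term. Secondary outcomes are to be analysed with similar models. Section 3.7 defines the primary outcome as the change in HAMD-24 from T0 to T1.

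**The concern.** The same measurement enters the model twice, with two consequences.

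First, the parameter named as the main one cannot benefit from the covariate. The stated reason for including it, better precision and control of baseline imbalance, fails for exactly the contrast on which the trial is to be judged.

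Second, the covariate does change the adjusted between-group difference at T1. The T0 rows fit themselves too well, the random-intercept model pools their small residual variance with that at T1 and T2, and the standard error at T1 is understated.

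One model would then yield two different answers for the primary endpoint. One is valid but inefficient. The other is anti-conservative, and could be reported as the trial result.

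**Working it through.** **Inputs.** From section 3.4: difference 4.34, pooled SD 5.21, two-sided alpha 0.05, 90% power, 32 evaluable per arm. The correlation ρ between visits is not given. It is an assumption here, taken as equal across visits and ranged from 0.2 to 0.8.

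**The plan's own figure.** The normal approximation gives 2 × (1.96 + 1.2816)² × 5.21² / 4.34² = 30.3, so 31 per arm. The noncentral t gives 32 (power 0.907). Then 32 / 0.90 = 35.6, so 36 per arm. The stated sample size reproduces; it rests on an unadjusted comparison of post-intervention means.

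**Step 1: the interaction.** Let D0 and D1 be the between-arm differences at T0 and T1. The T1 interaction contrast is D1 − D0. A term b × T0 is identical in every row of a subject and drops out. Section 3.11 plans multiple imputation, so each analysed data set is balanced and the point estimate is unaffected exactly. In one simulated data set fitted by REML, the T1 interaction was −4.2466 (SE 1.1865) both with and without the covariate, and equalled the raw difference in change scores.

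- SE of the interaction: 5.21 × √(2(1 − ρ) × 2/32)
- SE of ANCOVA at T1: 5.21 × √((1 − ρ²) × 2/32)
- Variance ratio: 2(1 − ρ)/(1 − ρ²) = 2/(1 + ρ)

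Power for 4.34 points, by normal approximation:

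| ρ | Interaction SE | ANCOVA SE | Variance ratio | Power, interaction | Power, ANCOVA |
|---|---|---|---|---|---|
| 0.3 | 1.54 | 1.24 | 1.54 | 80.4% | 93.7% |
| 0.5 | 1.30 | 1.13 | 1.33 | 91.5% | 97.0% |
| 0.7 | 1.01 | 0.93 | 1.18 | 99.0% | 99.7% |

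**Step 2: the adjusted difference at T1.** Set the variance to 1.

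- The fitted baseline slope comes from regressing the subject mean of all three rows on T0: b = (1 + 2ρ)/3, where ANCOVA would give ρ.
- The estimate is D1 − b × D0, with true variance factor 1 + b² − 2bρ.
- The model takes the residual variance as 1 − ρ and the intercept variance as (1 − ρ)(4ρ − 1)/9 (bounded at zero below ρ = 0.25). Their sum is the model's variance factor at T1.

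At ρ = 0.5: b = 0.667; true factor 1 + 0.444 − 0.667 = 0.778; model factor 0.5 + 0.056 = 0.556. Multiplying each square root by 5.21 × √(2/32) = 1.3025 gives a true SE of 1.149 and a model SE of 0.971.

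The source is the T0 row. Its residual variance is (1 − b)² = 0.111, against 0.778 at T1, about 14% as large.

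| ρ | Slope b | True SE | Model SE | Simulated 95% CI coverage |
|---|---|---|---|---|
| 0.3 | 0.533 | 1.279 | 1.102 | 91.0% |
| 0.5 | 0.667 | 1.149 | 0.971 | 90.1% |
| 0.7 | 0.800 | 0.939 | 0.782 | 90.4% |

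Coverage is from 8,000 simulated trials per row, 32 per arm, Satterthwaite degrees of freedom. A separate set of 20,000 null trials per correlation rejected in 8.9%, 10.0% and 10.2%. In closed form the model SE is 13 to 17% too small over ρ = 0.2 to 0.8. With correlations that decay over time, or a baseline SD 0.7 times that at later visits, coverage was 89.4 to 92.1%. In the same simulations the interaction's interval covered 94.3 to 95.9%, and ANCOVA at T1 95.0 to 95.2%.

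**Step 3: side by side.** The data set in step 1 shows the conflict. The planned model gives −4.25 (SE 1.19) as the interaction and −4.09 (SE 0.89) as the adjusted T1 difference. Using T1 and T2 rows only, with baseline as covariate, gives −4.01 (SE 1.01).

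**The case against.** The strongest defence is that the declared inference is sound. The interaction is the named parameter, it estimates the T0-to-T1 change that section 3.7 defines as primary, and its error rate stays close to 5%. A difference in change scores is a legitimate analysis. Section 3.4 took no credit for baseline adjustment, and at ρ = 0.5 the interaction still reaches the 90% target. The article also does not say that the reported mean differences are between-arm differences at T1.

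Much of this stands. The under-coverage belongs to the adjusted T1 difference and not to the interaction, whose fault is inefficiency. The power shortfall depends on an undocumented correlation and appears at lower values: 86% at ρ = 0.4, 80% at 0.3. The interaction's standard error is also not strictly untouched. When the covariate drives the estimated intercept variance to zero (about 36% of simulated data sets at ρ = 0.3, 5% at 0.5) it shifts, but by under 1% on average.

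It does not remove the point. The covariate is included for a purpose it cannot serve for the named parameter. Between-arm marginal mean differences with intervals and p-values are the natural reading of the promised output, and at T1 those are wrong. That the secondary outcomes are labelled exploratory lessens the weight of the fault there, but does not correct their intervals.

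**Conclusion.** The concern holds. As written, the baseline covariate does nothing for the group-by-time interaction and makes the adjusted T1 mean difference anti-conservative, with about 9 to 10% type I error and 90 to 91% coverage at equal correlations of 0.3 to 0.7. The first part is algebra and needs no assumption about ρ. The size of the second depends on the assumed correlation, but the direction was the same in every scenario examined. The interaction stays valid, at the cost of 1.54 (ρ = 0.3) to 1.18 (ρ = 0.7) times the variance of ANCOVA. The sample size calculation itself is not in question. Because the fault lies in the primary model and can produce an invalid p-value for the primary endpoint, it should be corrected before the data are analysed.

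**What to change.** Use T0 once.

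- **Preferred:** take T1 and T2 as the responses, with fixed effects for group, time, group-by-time, baseline and baseline-by-time. Name the adjusted group difference at T1 as the primary estimate. Given adjustment for T0, the group difference in the T1 score equals that in change from T0, so the primary outcome in section 3.7 is unchanged.
- **Alternative:** keep T0 as a response, constrain both arms to a common T0 mean, and drop the baseline covariate. This agrees closely with the preferred form only under a suitable covariance structure, such as an unstructured one. A random intercept alone does not guarantee it.

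Apply the same form to HAMA-14, CDI, MoCA and the HRV indices. The cost is a change of analysis wording; no extra participants, visits or data are needed.

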All efficacy analyses will follow the intention-to-treat (ITT) principle. Missing data will be handled using multiple imputation under the missing at random (MAR) assumption. The imputation model will include treatment allocation, demographic characteristics, baseline outcome values, and available follow-up measurements. Results from the multiply imputed datasets will be combined according to Rubin’s rules. Sensitivity analyses will be conducted to assess the robustness of the primary findings. Specifically, complete-case analysis and per-protocol analysis (including only participants who completed the intervention as planned) will be performed, and the results will be compared with those from the primary ITT analysis. For categorical outcome measures, between-group differences will be analyzed using chi-square tests or logistic regression models, as appropriate.

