Finally, participants will be followed up for 3 months after the intervention, with follow-up assessments conducted at 1, 2, and 3 months after discharge. The primary aim of the follow-up is to assess the short- to intermediate-term maintenance of treatment effects on depressive symptoms, autonomic function, cognitive function, and related psychological outcomes. The three-month follow-up period was chosen based on both methodological and practical considerations. On the one hand, this study aims to examine the immediate, short-term, and intermediate-term effects of the VR intervention rather than long-term relapse prevention. On the other hand, the study population consists of hospitalized adolescents with depression; longer follow-up periods may be associated with increased dropout rates as participants return to school or community settings after discharge. Therefore, this study is not intended to determine long-term sustainability of treatment effects, relapse rates, or relapse prevention outcomes beyond the three-month observation period. Any benefits observed during the 3-month follow-up should be interpreted as evidence of short- to intermediate-term maintenance rather than long-term efficacy. Future studies with longer follow-up periods (e.g., 6–12 months) are needed to assess the durability of treatment effects and their potential impact on relapse prevention.

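### Neither named sensitivity analysis relaxes missing at random, so their agreement with the primary result cannot show robustness to informative dropout; one tipping-point analysis at T1 would fill the gap

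*Protocol article*

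**What the plan says.** Section 3.11 (Statistical analysis) sets the handling of missing data for the intention-to-treat analysis: "Missing data will be handled using multiple imputation under the missing at random (MAR) assumption". Results are pooled by Rubin's rules. It lists the contents of the imputation model: "The imputation model will include treatment allocation, demographic characteristics, baseline outcome values, and available follow-up measurements".

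On robustness it says "Sensitivity analyses will be conducted to assess the robustness of the primary findings", and then fixes what these are: "Specifically, complete-case analysis and per-protocol analysis (including only participants who completed the intervention as planned) will be performed". Their results are to be compared with the primary analysis. No delta-adjusted, reference-based, pattern-mixture or selection-model analysis is mentioned.

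Three other places bear on the point:

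- Section 3.4 (Sample size) gives the only dropout figure: "Accounting for a potential dropout rate of 10%, the final sample size was increased to 36 participants per group".
- Section 3.9 (Retention and follow-up) plans to seek primary outcome data from participants who stop the intervention, and to record why people drop out.
- Table 1 in section 3.8 shows no HAMD-24 assessment between T0 and T1.

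**The concern.** A sensitivity analysis for missing data should vary the assumption on which the primary analysis depends. Here that assumption is that, given arm, baseline, demographics and other available measurements, a participant with a missing score resembles one whose score was observed.

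Complete-case analysis does not loosen it. With missing outcomes it needs data missing completely at random, or missingness that depends only on the covariates in the model. Per-protocol analysis selects on completing the intervention, which happens after randomisation. It answers a different question and leaves the missing-data assumption untouched.

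There is reason to want the assumption tested. Participants know their allocation (section 3.5), and section 3.12 describes a route to stopping sessions, for discomfort, that exists only in the VR arm. With no rating between T0 and T1, a VR participant who leaves early and is never rated again is imputed from arm, baseline and demographics, and so is credited with the result of similar VR participants who stayed. If such people actually did worse, the benefit is overstated. Because complete-case analysis errs in the same direction, the planned comparison would look reassuring.

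**Working it through.** **Inputs.** From section 3.4: difference 4.34 points (25.64 - 21.30), SD 5.21, 36 randomised and 32 expected completers per arm, 10% dropout. From section 3.11: two-sided 5% level. Assumed here: baseline-to-T1 correlation 0.5, and every missing rate above the planned level.

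**1. The plan's own figure.** Pooled SD = sqrt((5.03² + 5.39²)/2) = 5.21. For 90% power the normal formula gives 30.3, so 31 per arm; the t-based calculation gives 31.28, so 32. Then 32/0.9 = 35.6, so 36. The stated 32 and 36 reproduce.

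**2. Can the complete-case comparison detect informative dropout?** Large-sample simulation, 400,000 per arm, true difference -4.34. Control dropout is random. VR dropout depends on the unobserved T1 score through a logistic model, with slope 1 per SD (moderate) or 2 (strong). MAR imputation is represented by regression on baseline within arm. Estimated differences:

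| Dropout | Dependence | MAR imputation | Complete-case, baseline-adjusted | Complete-case, unadjusted |
|---|---|---|---|---|
| 10% | none | -4.36 | -4.35 | -4.36 |
| 10% | moderate | -4.73 | -4.71 | -4.84 |
| 10% | strong | -4.94 | -4.92 | -5.10 |
| 20% | none | -4.36 | -4.35 | -4.36 |
| 20% | moderate | -5.06 | -5.04 | -5.26 |
| 20% | strong | -5.45 | -5.40 | -5.72 |

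The adjusted complete-case estimate stays within 0.05 of the MAR estimate throughout, whether the MAR estimate is right or about 1.1 points too favourable. Agreement between them carries no information on this question. Per-protocol analysis was not simulated; the point about it is one of definition.

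**3. Size of the shift at T1.** If missing VR scores are k points worse than imputed and a fraction f of the VR arm is missing, the difference shrinks by f × k. With f = 0.10 and k = 5 the shift is 0.5 point, which is 0.5/4.34 = 12% of the planned effect.

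**4. Penalty at which significance is lost, at the planned effect.** SE held at the completers' value.

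- Baseline-adjusted: SE = 5.21 × sqrt(1 - 0.5²) × sqrt(2/32) = 1.13. Smallest significant difference about 2 × 1.13 = 2.26. Penalty = (4.34 - 2.26)/0.10 = 20.8 points.
- Unadjusted: SE = 5.21 × sqrt(2/n), threshold = t × SE, f = 1 - n/36:

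| Completers per arm | Missing | SE | Threshold | Penalty at loss of significance |
|---|---|---|---|---|
| 32 | 11% | 1.30 | 2.60 | (4.34 - 2.60)/0.111 = 15.6 |
| 29 (assumed) | 19% | 1.37 | 2.74 | (4.34 - 2.74)/0.194 = 8.2 |
| 25 (assumed) | 31% | 1.47 | 2.96 | (4.34 - 2.96)/0.306 = 4.5 |

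**5. A smaller observed effect.** With an observed difference of 2.75 (illustrative), the adjusted threshold and 10% missing, the penalty is (2.75 - 2.26)/0.10 = about 5 points.

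**The case against.** The strongest reply is that the primary conclusion is not fragile as planned. About four participants per arm are expected to be missing, and overturning a 4.34-point effect would take a penalty of 3 to 4 SD (15.6/5.21 = 3.0; 20.8/5.21 = 4.0). This stands, and it limits the weight of the point.

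Stopping VR is also not the same as a missing outcome. Participants are inpatients, T1 follows the intervention immediately, inability to tolerate VR equipment is an exclusion, and section 3.9 seeks outcome data after discontinuation. Someone who stops sessions because of nausea can still be rated. This reduces the risk without guaranteeing retrieval. The documents do not record why participants would leave, so informative dropout is a plausible risk and not an established one.

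An analysis plan that is not shown might add the missing analysis. That is possible, but the article does not leave the choice open: it names the two analyses that are to serve as the robustness check, and the criticism is of that choice.

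Two stronger readings are tempting and should be resisted. A reader might infer that the protocol claims robustness to informative dropout. It does not: it says only that robustness will be assessed, and never mentions informative dropout. A reader might also take the Discussion as forecasting heavy loss by T2, because it says "longer follow-up periods may be associated with increased dropout rates as participants return to school or community settings after discharge". That sentence explains why follow-up was not extended beyond three months. It gives no rate within the planned follow-up, and no T2 dropout figure appears anywhere.

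**Conclusion.** The point holds as a bounded gap in the pre-specified robustness check. Neither named analysis relaxes MAR, and the complete-case result would track the primary result under informative VR-arm dropout, so their agreement should not be read as evidence against it.

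At the planned effect and about 10% missing, the effect on T1 is modest: 0.5 point for a 5-point penalty, with significance lost only at about 15.6 to 20.8 points. The lower figure uses the unadjusted SE and 11% missing; the upper uses an assumed correlation of 0.5 and 10% missing. Both apply the penalty to the VR arm only and hold the SE fixed. A reader should not infer that the primary result is likely to be overturned. The gap becomes material if the observed effect is well below 4.34 points or if missingness exceeds the planned rate. Neither can be known in advance, which is the reason to specify the analysis now.

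**What to change.** Keep the complete-case and per-protocol analyses. In section 3.11, add one delta-adjusted tipping-point analysis of the T1 HAMD-24 contrast on the same imputed datasets: add 0, 1, 2 and so on points to the imputed VR-arm T1 values, refit the primary model, pool by Rubin's rules, and report the penalty at which significance is lost. State that this analysis addresses departures from MAR, and describe the other two by what they do address.

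A control-based imputation and a repeat at T2 are optional.

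The cost is a little extra programming: a conditional shift of values flagged as imputed and a loop over penalties. It needs no further data, visits or participants, and leaves the primary analysis unchanged.
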